**Figure 1 figure1:**

Participant flow. EMA: ecological momentary assessment.

Following the completion of the smartphone-based baseline assessment in phase 2, we will block randomize participants by binary sex (assigned at birth) and baseline smoking level (rate per day) to ensure that the cell sizes are largely equivalent for maximally useful subgroup testing [67]. Variable-sized permuted block randomization (block sizes will vary from 6 to 10) will be used. Before data analysis, the balance of randomization will be checked and controlled for imbalanced factors.

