**Methods:**

In phase 1, a total of 25 Black smokers with elevated AS will be administered MASP for 6 weeks. Following the completion of phase 1, we will further refine the MASP based on qualitative and quantitative data from participants to produce the final MASP iteration. In phase 2, a total of 200 Black smokers with elevated AS will be enrolled and randomly assigned to receive nicotine replacement therapy and either the smartphone-based National Cancer Institute QuitGuide app for standard mobile smoking cessation treatment or the MASP intervention. All participants in phases 1 and 2 will be enrolled remotely and will complete a web-based study screener; smartphone-based baseline assessment; daily smartphone-based ecological momentary assessments for 6 weeks; phone-based end-of-treatment qualitative interviews; and smartphone-based follow-up assessments at postbaseline weeks 1, 2 (quit date), 3, 4, 5, 6, 28, and 54 (weeks 28 and 54 follow-ups will be completed by phase 2 participants only). The MASP intervention is intended to offset barriers to treatment and encourage treatment engagement via smartphones.

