To date, no smoking cessation treatments for Black smokers have focused on sensitivity to interoceptive stress despite the importance of somatic symptoms, including anxiety, stress, and pain, among this population. Furthermore, previous efforts to evaluate the effectiveness of culturally targeted smoking cessation programs for Black smokers have mainly used minimal intervention strategies and group counseling and were nonrandomized trials [59]. We developed and preliminarily tested our novel, integrated, smartphone-delivered intervention for interoceptive stress and smoking (ie, Mobile Anxiety Sensitivity Program for Smoking [MASP]) using a single-arm pilot trial design [57]. This intervention is based on theory and empirical evidence of the importance of interoceptive stress for smokers [60]. The purpose of our initial pilot of the MASP 1.0 (N=12; mean age 45 years; 66.7% Black) was to assess app engagement and determine whether there was an initial signal of app impact on cessation. Participants self-initiated interoceptive exposure exercises 6 times on average, self-initiated *relaxation exercises* 6 times on average, and accessed *treatment audio files* 2 times on average [57]. Biochemically verified abstinence was observed in 25% of the participants at the 6-week follow-up visit (4 weeks after quitting), which are striking and clinically important, given that (1) this was only the initial version of the treatment (MASP 1.0), and (2) smoking cessation success rates for Black smokers are typically low.

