### Study Eligibility

Adults aged ≥18 years are eligible to participate in this study if they self-identify as Black and report high AS (ie, Short Scale Anxiety Sensitivity Index [64] score of ≥5), daily smoking (minimum of 10 cigarettes per day) for at least 2 years, motivation to quit smoking (>5 on a 10-point scale) [65], willingness to complete all study surveys and assessments, willingness to use nicotine replacement medications (nicotine replacement therapy [NRT]; nicotine patch and lozenges), and desire to quit smoking 2 weeks after completion of the baseline survey and receipt of study materials. The exclusion criteria include current or intended participation in a concurrent substance use treatment program, ongoing psychotherapy of any duration directed specifically toward the treatment of anxiety or depression, not being fluent in English, current use of any pharmacotherapy or psychotherapy for smoking cessation not provided by this study, a legal status that would interfere with participation, cognitive impairment (assessed via the 6-item Cognitive Impairment Test [66]), being non-Black, and being aged <18 years. Those who participated in the previous phase of the study are not eligible to participate in future study stages.

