#### Smoking Outcomes

Biochemically confirmed smoking status will be assessed 3 times per week using the Insight platform (phases 1 and 2). Consistent with most published smoking cessation RCTs (see the Clinical Practice Guidelines) [68] and best practices (see the study by Benowitz et al [105]), our primary study outcome is the biochemically confirmed, 7-day, point prevalence abstinence (PPA) 4 weeks (phase 1) or 52 weeks (phase 2) after the scheduled quit date. Secondary outcomes (eg, time to first lapse and longest time of quitting) will also be examined. Smoking abstinence will be assessed daily via self-report (ie, EMA; weeks 1-6, 28, and 54 [phase 2 only]). The low-cost Bedfont iCOquit smokerlyzer will be used to verify smoking status during the follow-up assessments (ie, quit date; weeks 1-4, 26, and 52 after quitting). Participants will be prompted by the Insight app to connect the iCO device to the smartphone (simply by pushing the power button) and follow step-by-step directions to complete the iCO test. The results of these tests will be automatically date- and time-stamped and saved to our server. We have integrated automated and secure (ie, encrypted) facial recognition software to ensure that only the participants complete the prompted iCO tests. Our CO criteria for abstinence is consistent with numerous studies using cutoffs <7 ppm [106-112]. The half-life of CO is up to 8 hours, depending on a variety of factors (eg, time of day and daily smoking rate) [113]. Expired CO is a valid indicator of smoking status and cessation outcomes and compares favorably with cotinine and other biochemical measures that have longer detection windows [114-116].

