Multiple approaches to modeling changes in abstinence will be used to evaluate our primary hypothesis that the MASP 3.0 will result in higher rates of smoking abstinence relative to the NCI QuitGuide app. We will first use the biochemically verified measure of 7-day PPA, which will be collected via Bedfont iCO at each major assessment, as the primary indicator of abstinence. PPA will be defined as no smoking, not even a puff, in the 7 days before any assessment. We will estimate between-group differences by calculating the odds ratio effect sizes (with 95% CIs) for PPA at each follow-up assessment. We will then conduct a series of conditional latent growth models to examine the impact of treatment conditions on abstinence trajectories. We will use multilevel structural equation models to examine the effects of the MASP 3.0 intervention on the longitudinal course of smoking behaviors, as measured by daily dairy and random sampling EMA data. We will conduct survival analyses using Cox proportional hazard models to assess time to lapse and time to relapse and whether the treatment condition predicts patterns of smoking in survival analysis. Similar modeling procedures will be used to determine the impact of treatment conditions on AS, anxiety symptoms, depression symptoms, stress burden, nicotine withdrawal, and craving and whether improvements in smoking cessation outcomes are mediated by reductions in AS and secondary mechanisms.

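### Covariates are to be picked by observed baseline imbalance, a rule that in effect leaves out the two stratification factors and lets chance decide which others enter

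*Protocol article*

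**What the plan says.** All of this concerns the phase 2 randomized comparison in the protocol article.

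- **Randomization** (Methods, Recruitment and Procedure, paragraph below Figure 1): "we will block randomize participants by binary sex (assigned at birth) and baseline smoking level (rate per day"). The blocks are permuted: "Variable-sized permuted block randomization (block sizes will vary from 6 to 10) will be used". No cut points for smoking level are given.
- **Covariate rule** (same paragraph): "Before data analysis, the balance of randomization will be checked and controlled for imbalanced factors". No other covariate rule appears in the article.
- **Effect measure** (Statistical Analyses): "We will estimate between-group differences by calculating the odds ratio effect sizes (with 95% CIs) for PPA at each follow-up assessment". No covariates are named there.
- **Primary endpoint** (Smoking Outcomes): biochemically confirmed 7-day "point prevalence abstinence (PPA) 4 weeks (phase 1) or 52 weeks (phase 2) after the scheduled quit date", which for phase 2 is the week-54 assessment.

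The article neither commits to adjusting for the stratification factors nor forbids it.

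**The concern.** The rule and the design pull against each other. Stratified blocking is there to make the arms alike on sex and smoking level. A rule that adjusts only for what turns out unlike then passes over those two factors because the blocking worked. But blocking on a prognostic factor removes its contribution to the variability of the treatment difference, and an analysis that ignores the factor still counts that contribution as noise. If the factor predicts abstinence, the unadjusted test is conservative and some of the benefit of stratifying is wasted.

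For every other baseline variable the rule selects on chance difference rather than on relation to outcome. With no criterion stated, two analysts could reach different models from the same data. Running the check before the analysis does not settle this, because what counts as imbalanced is still open at that point.

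**Working it through.** The article gives no power statement, expected effect or dropout, so there is no figure to reproduce.

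**Inputs from the article.** Phase 2 total: "a total of 200 Black smokers with elevated AS will be enrolled and randomly assigned". Stratification factors, block sizes and endpoint are as above. The only abstinence rate is from the single-arm pilot (N=12), four weeks after quitting: "Biochemically verified abstinence was observed in 25% of the participants at the 6-week follow-up visit". Smoking level is truncated from below at entry: "daily smoking (minimum of 10 cigarettes per day) for at least 2 years".

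**Assumptions.** 1:1 allocation (100 per arm), 2×2 strata of equal expected size, blocks of 6, 8 and 10, two-sided 5% (implied by the 95% CI), control abstinence of 10% or 20% at week 54, no dropout. Odds ratios (ORs) linking sex and smoking level to abstinence are not given, so a range is used.

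**1. Would the rule select the strata?** In simulation (6,000 trials per scenario), both factors as stratified were flagged in 0% of trials at p<0.05, and in at most 0.1% at a standardized difference above 0.1. Cigarettes per day checked as a continuous variable was flagged in about 0.4% at p<0.05, but in about 32% at a standardized difference above 0.1.

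**2. Would it select something else?** The Baseline Assessment section lists about 25 constructs. Treating factors as independent, the chance of at least one flag at p<0.05 is 1 − 0.95^K: 40% for K=10, 64% for K=20, 72% for K=25.

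**3. Cost of leaving out the strata (formula).** Let R² be the between-stratum share of outcome variance, i.e. the variance of the stratum rates divided by p(1−p). With the strata balanced by design:

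- type I error of the unadjusted test = 2[1 − Φ(1.96/√(1−R²))]
- its power, where the adjusted test has 80%, = Φ(1.96 + 0.84 − 1.96/√(1−R²))

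Example: control rate 20%, factor ORs 2 and 3. The stratum rates are 0.351, 0.153, 0.213 and 0.083, so R² = 0.061 and 1.96/√0.939 = 2.023. Type I error is 4.3% and power is Φ(2.80 − 2.02) = 78.2%.

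| Factor ORs | Control rate | R² | Type I error | Power (adjusted = 80%) |
|---|---|---|---|---|
| 1.5, 1.5 | 10% / 20% | 0.007 / 0.013 | 4.9% / 4.9% | 79.8% / 79.6% |
| 1.5, 2 | 10% / 20% | 0.014 / 0.025 | 4.8% / 4.7% | 79.6% / 79.3% |
| 2, 3 | 10% / 20% | 0.035 / 0.061 | 4.6% / 4.3% | 79.0% / 78.2% |
| 3, 4 | 10% / 20% | 0.062 / 0.106 | 4.3% / 3.8% | 78.2% / 76.7% |

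**4. Same question by simulation** (Monte Carlo SE about 0.6 points for power, 0.3 for type I error):

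| Control rate, treatment OR | Factor ORs | Chi-square, unadjusted | Mantel-Haenszel by strata | Logistic LR, unadjusted | Logistic LR, adjusted |
|---|---|---|---|---|---|
| 10%, 2.8 | 1, 1 | 75.9% | 75.5% | 75.9% | 76.4% |
| 10%, 2.8 | 1.5, 2 | 73.3% | 73.9% | 73.5% | 74.8% |
| 10%, 2.8 | 2, 3 | 69.2% | 70.7% | 69.4% | 71.7% |
| 10%, 2.8 | 3, 4 | 65.2% | 68.1% | 65.3% | 69.3% |
| 20%, 2.4 | 1.5, 2 | 76.3% | 77.2% | 76.5% | 77.8% |
| 20%, 2.4 | 2, 3 | 71.9% | 74.1% | 72.0% | 74.7% |

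With prognostic strata, adjustment gains 0.5 to 2.9 points (Mantel-Haenszel) or 1.3 to 4.0 points (logistic). Simulated type I error in the two stronger settings was 4.0–4.6% unadjusted and 4.8–5.1% with Mantel-Haenszel. The 20% control rate with factor ORs 3 and 4 was not completed in that simulation and rests on the formula.

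**5. Effect of the selection step itself.** Take one unstratified covariate that explains 10%, 20% or 30% of outcome variance and is adjusted for only if imbalanced at p<0.05. Type I error is then 4.7%, 4.5% or 4.1%: again conservative.

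**The case against.** The best defence is that the article condenses a fuller plan. It does not call the odds ratios unadjusted, and it does not say that only imbalanced factors may enter. The stratification is motivated by subgroup testing, so the team clearly means to use these factors, and a primary-model covariate list normally sits in an analysis plan, which is not shown here. This stands as far as it goes: a missing list would be no finding. But the imbalance rule is stated, not missing, and an analysis plan that fixed the strata as covariates would have to supplement or override it.

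Four stronger readings are tempting and are not supported.

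- **The strata can never be selected.** This fails for cigarettes per day checked as continuous against a lenient threshold (step 1).
- **The trial certainly loses calibration and power.** The loss depends on prognostic strength, which the article does not give.
- **Type I error drops well below 5% because of the rule.** A logistic Wald test in this design rejects only 3.9% (10% abstinence) or 4.5% (20%) even when the strata are unrelated to outcome. That part is small-sample conservatism of the Wald test. Nothing in the check shows inflation above 5%.
- **Adjustment will narrow the reported interval.** For a logistic odds ratio it does the opposite. In one setting (control rate 20%, OR 2.4) the standard error of the log odds ratio was 0.339 adjusted and 0.327 unadjusted. Power rises because the conditional odds ratio lies further from 1, and it is a different quantity from the marginal one.

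**Conclusion.** The point holds as a poorly chosen stated method with a modest cost. Covariates are selected by chance imbalance with no criterion, and the rule almost never picks the stratification factors as stratified, so the week-54 comparison as written does not account for the randomization strata.

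If the strata predict abstinence, the unadjusted test is mildly conservative. For modest predictors (ORs 1.5 to 2) the loss is under about 0.4 points of type I error and about 1 point of power. For the strongest pair examined (ORs 3 and 4) it is about 1 point of type I error and about 3–4 points of power in simulation; the formula gives 1.8–3.3 points of power at an 80% reference. If the strata are not prognostic, nothing is lost. These sizes rest on the assumptions listed in the check, above all the 10–20% control rates and the prognostic ORs. The open choice of model does not depend on them.

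Label: free improvement.

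**What to change.** Replace the imbalance sentence with a fixed rule:

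- The primary week-54 abstinence model includes treatment, sex and baseline smoking level (as stratified or continuous, chosen now), whatever the observed balance.
- Any further prognostic baseline covariates are named before unblinding. Candidates already collected include heaviness of smoking and anxiety sensitivity, though the article does not quantify how well either predicts week-54 abstinence.
- Baseline balance is reported descriptively only and does not change the model.
- The adjusted odds ratio is stated to be conditional on these covariates, or a standardized marginal effect is reported alongside it.

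The cost is a few lines of text. No new data, visits or participants are needed. If a fuller analysis plan already fixes these covariates, it is enough to bring the article's sentence into line with it.

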### Study Conditions

#### Both Conditions

Clinical guideline recommendations indicate that all smokers attempting to quit should receive pharmacotherapy [68]. Thus, the MASP (phases 1 and 2) and QuitGuide (phase 2) participants will receive a combination of NRT (transdermal nicotine patch and nicotine lozenges) during the first 4 weeks after quitting. Additional NRT (up to 8 additional weeks) may be requested beyond the first 4 weeks by clicking a button on the app home screen or clicking the *Call Staff* button on the app home screen (Figure 2). Note that 66% of those enrolled in one of our previous studies used a similar app button and feature to order the NRT [62]. We chose the patch and lozenges because of the extensive empirical literature supporting their effectiveness and safety, ease of use, and relatively benign side effect profile, as well as the increased efficacy of combination NRT [69,70]. The MASP app will send an encrypted email to alert the treatment team of NRT requests, and participants will be mailed an additional NRT.

**Figure 2 figure2:**
[figure not shown]
The Mobile Anxiety Sensitivity Program for Smoking app.

#### NCI QuitGuide Condition

The NCI QuitGuide app is a free smartphone app available through Smokefree.gov. QuitGuide is one of the few apps that are consistent with many of the recommendations of the Clinical Practice Guidelines for quitting smoking [68]. Individual-level app feature use is accessible by request from Smokefree.gov server. The QuitGuide app aims to help smokers understand their smoking patterns and develop the skills needed to quit smoking. Participants who are randomly assigned to the QuitGuide condition will use their personal smartphone or receive a study smartphone if they do not have one, which will be preloaded with the QuitGuide app and preset for a quit date 2 weeks after randomization into an intervention group. Participants will receive information on how to use the QuitGuide app features during the randomization phone call. QuitGuide participants will also download an Insight EMA app stripped of all the MASP intervention features. Table 1 for a list of QuitGuide features.

**Table 1 table1:** Comparison of phase 2 treatment conditions.

App components			MASP^a^		QuitGuide
EMA^b^			✓		✓ (add-on for this study)
Set a quit date			Quit date set to 2 weeks after randomization and receipt of the iCO via mail		Quit date set to 2 weeks after randomization and receipt of the iCO via mail
Share quit information on social media					✓
Smoking cessation psychoeducation			✓		✓
Content specific to Black smokers			✓		
NRT^c^ tips and use advice			✓		
AS^d^ psychoeducation			✓		
**On-demand tips and exercises**					
	Coping with cravings	✓		✓	
	Coping with mood	✓		✓	
	Coping with stress	✓			
	Inspirational messages	✓		✓	
Scheduled tips					✓
Treatment messages tailored to currently present smoking lapse triggers			✓		
**Coping toolkit**			✓		
	Guided relaxation and mindfulness exercises	✓			
	Challenging automatic thoughts	✓			
	Tips for coping with stress	✓			
	Interoceptive exposure	✓			
	Resources to help distract participants if they experience elevated distress	✓			
Individualized quit plan					✓
Document smoking triggers					✓
List reasons for quitting					✓
Saving from smoking fewer cigarettes					✓
Creating journal entries					✓

^a^MASP: Mobile Anxiety Sensitivity Program.

^b^EMA: ecological momentary assessment.

^c^NRT: nicotine replacement therapy.

^d^AS: anxiety sensitivity.

#### MASP Condition

##### Overview

The updated MASP 2.0 app focuses on general interoceptive stress-related issues and interoceptive stress that may be specific to Black smokers [71]. The MASP 2.0 integrates a standard cognitive behavioral therapy smoking cessation protocol (clinical practice guidelines) [68] with transdiagnostic treatment for AS reduction in a culturally adapted framework. Specifically, the MASP 2.0 provides (1) standard treatment on a schedule, (2) scheduled and cued interoceptive exposure sessions, (3) personalized and tailored messaging after each EMA (before and after quitting), and (4) *on-demand* features (eg, coping toolkit and cognitive restructuring exercises) before and after quitting. Culturally specific elements (eg, education about menthol tobacco products, history of tobacco marketing to Black smokers, concerns about pharmacotherapy, religion and spirituality coping, and the impact of racism and racial discrimination on stress and smoking) are included throughout the MASP 2.0.

##### Treatment on a Schedule

The MASP 2.0 includes 16 intervention videos of 4 to 6 minutes (adapted from traditional AS reduction treatments [72] and the MASP 1.0 audio files), which are delivered through the MASP 2.0 app over the 6-week intervention period. Notably, Black voice actors (men and women) will present all intervention content. New videos will be offered at the completion of the prequit morning and evening EMAs. Participants will have the option to watch videos immediately or later by clicking the on-demand *Treatment Videos* button (Figure 2). Videos can be watched as many times as desired, and the app records the date, time and location when each video is watched (both initiation and completion).

The brief videos provide psychoeducation on multiple topics, including the relationship between stress and smoking, managing uncomfortable sensations, unhelpful thinking, smoking as a temporary coping mechanism to avoid experiencing negative emotions, thinking flexibly, myths about smoking, coping with others smoking nearby, nicotine withdrawal, the importance of using NRT, stress management, interoceptive exposure techniques, and strategies for cessation and relapse prevention. Culturally tailored content (eg, tobacco industry marketing of menthol cigarettes to Black communities, effects of discrimination on smoking and relapse, concerns about pharmacotherapy, chronic stress and race, and the role of AS in interoceptive stress in Black adults) is infused throughout the brief videos.

##### Exposure Sessions

Internet-based interoceptive exposure is well-tolerated, acceptable, and effective [73,74]. To target AS, graduated exposure to anxiety- and distress-provoking situations and response prevention is introduced in the MASP videos. These exposure exercises were created for the MASP 1.0 study (ie, overbreathing, straw breathing, running in place, chair spinning, and head rush) [57]. The app reminds participants of the importance of completing the exposure sessions 3 times per day during random EMAs. Participants will be instructed to click the *Stress Management Trainings* button to initiate an interoceptive exposure session (Figure 2). The MASP app randomly selects 1 of the 5 exercises each time the *Stress Management Trainings* button is pressed. The participants will be guided through interoceptive exposures by explaining the purpose of the activity and how to perform it, normalizing the physical symptoms experienced during the exercise and relating this experience to the process of quitting smoking (eg, tolerance of physical symptoms related to anxiety, discrimination, and withdrawal). As in the MASP 1.0 pilot [57], when the participant is ready to begin, the app assesses the level of distress (0-100 scale), shows a countdown timer while the exercise is being completed, and assesses the level of distress again (0-100 scale) once the countdown expires. The app suggests repeating the exercise up to 3 additional times if the current reported distress is >50 on a 1 to 100 scale. This strategy aims to increase habituation to feared sensations. In the MASP pilot study [57], participants accessed the stress management training exercises on 6 of the 13 days that preceded their quit date.

